#### Confidence in providing Mental Health First Aid for a person with depression or psychosis

Participants will also be asked to rate their confidence in supporting the person in each of the vignettes (1=not at all confident to 7=extremely confident).

#### Helping actions taken to assist a person with a mental health problem

Participants will be asked about any helping actions taken to assist a person who is at risk of a mental health problem or crisis, using the MHSS-provided version that has been adapted and validated for Chile and Argentina. This scale has been shown to be a reliable and valid measure of help provided to a person the respondent knows well.^39^ It consists of 10 items (8 recommended, 2 not recommended) with a response scale of ‘Yes’ or ‘No’. Higher scores indicate better mental health support. Each factor of the MHSS provided for Argentina and Chile showed excellent internal consistency and the Recommended factor discriminated between those with and without mental health training.^38^

#### Desire for social distance from a person with depression and from another person with psychosis

Participants desire to avoid contact with a person with depression or with psychosis will be measured for each vignette. The Social Distance Scale includes five items measured on a 4-point Likert scale (1 =‘yes, definitely’ to 4=‘no, definitely not’).^43^ The scale asks: ‘Would you be happy to: 1) move next door to J/A? 2) spend an evening socializing with J/A? 3) make friends with J/A? 4) work closely with J/A on a project at work? 5) have J/A marry into your family?’ The measure has shown excellent reliability with α=0.88 in community questionnaires in Australia,^44^ and an acceptable reliability (α=0.78) in Chile.^45^ Furthermore, it has been extensively used in Argentina and Chile.^46^,^48^

#### Personal stigmatising attitudes about an individual with depression and another individual with psychosis

For each of the vignettes, participants will be asked to what extent they agree with nine statements designed to measure stigmatising attitudes (1=strongly disagree and 5=strongly agree). The stigma items will be based on the Depression Stigma Scale^49^ and a Chilean version of the scale used with adolescents.^50^

The scale includes the following statements: (1) People with a problem like [initials] could snap out of it if they wanted, (2) A problem like [initials]’s is a sign of personal weakness. (3) A problem like that of [initials] is not a real medical illness, (4) People with a problem like [initials]’s are dangerous to others, (5) It is best to avoid people with a problem like [initials] so that you do not develop this problem, (6) People with a problem like [initials] are unpredictable, (7) If I had a problem like [initials]’s I would not tell anyone, (8) I would not employ someone if I knew they had a problem like [initials]’s in the past and (9) I would not like my children to be looked after by a person like [initials]. The ‘initials’ will refer to a person with psychosis in the first place, and then would refer to a person with depression. The items form two scales ‘Weak not sick’ and ‘Dangerous/Unpredictable’ which have previously been shown to demonstrate high internal consistency in the English-language version.^44^

#### Course quality and satisfaction

In the first follow-up questionnaire (T2), participants in the intervention group will be asked about their satisfaction with the course and their opinions on its quality.^51^ A translated and adapted version of this questionnaire was used in the pilot MHFA training in Argentina and Chile. It includes sixteen items rated on a 4-point or 5-point Likert scale, assessing the usefulness, novelty and relevance of the content, as well as the course duration and participants’ preferences regarding different components (eg, manual, PowerPoint slides, videos and activities). Additionally, two open-ended questions explore which aspects of the course were most helpful and whether any improvements could be made.

The selection of intentions to provide MHFA as the primary outcome is consistent with prior evaluations of MHFA training.^32 52^ In line with MHFA being conceptualised as an intervention targeting mental health literacy, which comprises multiple distinct components,^26 53^ several secondary outcomes are included to capture these dimensions. These secondary outcomes will be treated as exploratory, and findings will be interpreted cautiously in light of the increased risk of type I error associated with multiple comparisons.

#### Power and sample size

According to the Shiny cluster randomised trial (CRT) calculator,^54^ with six clusters per arm (12 in total) the study will have 90% power, at a two-sided 5% significance level, to detect a standardised mean difference of 0.5 in intentions scores between intervention and control groups at 6-month follow-up. In the absence of pilot data, the sample size calculation assumed a conservative intracluster correlation coefficient of 0.05, equal cluster sizes, a correlation of 0.5 between individual measurements over time and a 30% loss to follow-up. The assumed effect size was informed by a meta-analysis of MHFA training, which found pooled effect sizes for intentions were d=0.75 immediately post training and d=0.55 up to 6 months after training.^26^

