**Methods and analysis:**

The study involves a two-arm wait-list cRCT with 240 participants (120 in each country). The study will be conducted in three settings in each of Chile and Argentina (eg, universities, health services and workplaces). Two clusters per setting in each country will be paired and randomly allocated to the intervention (the MHFA training for Chile and Argentina) or the wait-list control group. Participants in the intervention arm will be asked to complete questionnaires at baseline (T1), after training completion (T2) and 6 months after completion (T3), with control arm participants completing data collection at corresponding time points. The primary outcome will be intended support towards someone experiencing a mental health problem or experiencing a mental health crisis. Secondary outcome measures will include the ability to recognise depression and psychosis in vignettes; beliefs about the helpfulness of different types of interventions and helping actions, confidence in providing MHFA and stigmatising attitudes towards a person with depression or psychosis. Findings will demonstrate whether the culturally adapted MHFA training for Chile and Argentina can effectively enhance intended support, knowledge, attitudes and supportive actions towards other individuals within the community.

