## Methods and analysis

### Study design

A two-arm cRCT will be used to evaluate the effectiveness of MHFA training in Chile and Argentina. A cluster will be defined as a single training group (approximately 20 participants) recruited within one organisation in a given setting and country. Within each setting and country, two clusters will be paired, with one allocated to the intervention and one to the wait-list control group. The settings include universities (undergraduate alumni), healthcare personnel and corporate workplaces. Participants will be compared with a control group that will receive the training course after the study has been completed. To facilitate engagement and retention, the local research team will approach organisations that have expressed interest in receiving MHFA training. The settings were selected because they represent contexts in which community members are likely to encounter individuals experiencing mental health problems, and because MHFA is commonly implemented in similar settings internationally, supporting future scalability and implementation.

The trial aims to assess the impact of MHFA training for Chile and Argentina on: intended support for someone developing a mental health problem or in a mental health crisis; the capacity to recognise in a vignette whether someone is experiencing depression or psychosis; beliefs about the helpfulness of interventions for a mental health problem (ie, depression or psychosis); helping actions taken to assist a person in these situations; confidence in providing MHFA; stigmatising attitudes; and desire for social distance from a person with an affective mental health problem (ie, depression) or psychosis.

The trial coordinator will recruit participants in each country. Clusters from each setting will be paired and randomly allocated to the intervention (MHFA training in Chile and Argentina) or the wait-list control group, with a 1:1 allocation. Figure 1 illustrates the trial design, and figure 2 shows the timeline with enrolment and assessment points. The course will be delivered face-to-face.

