#### Statistical analyses

Statistical analyses will be conducted by a researcher not involved in participant recruitment or intervention delivery and blinded to allocation, following intention-to-treat principles; all participants who consent to participation will be included in the analysis, regardless of intervention completion or follow-up responses. Outcomes will be analysed at the individual level (rather than cluster level). Primary and secondary data will be analysed using mixed-effects models for continuous and binary outcome variables, incorporating interactions between group and measurement occasions. This method takes into consideration the data’s hierarchical structure (ie, the correlation of measurement occasions within participants and within clusters) and uses maximum likelihood methods to generate unbiased estimates even when some participants have missing data, provided that the data are missing at random. Country and setting will be added as fixed effects. Predictors of missingness will be examined using logistic regression, and variables linked to missingness will be added to models as fixed effects. Contrasts will compare change between groups from T1 to T2 and T3. Unless there are substantial imbalances at baseline, between-group effect sizes (Cohen’s d) will be calculated by standardising the differences between follow-up scores by the pooled SD. Otherwise, Cohen’s d will be calculated by dividing the mean change in each group by the pooled SD at baseline. Statistical analyses will be conducted using Stata V.19.^57^

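### The stated 90% power matches a baseline-adjusted analysis, but the planned test is a contrast of change, which gives about 75–87% on 10 df when the cluster autocorrelation is 0.8–1

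*Protocol article*

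**What the plan says.** The Power and sample size section claims that "with six clusters per arm (12 in total) the study will have 90% power, at a two-sided 5% significance level". The target is a 0.5 SD difference between arms in the primary outcome at T3. The inputs are an ICC of 0.05, described as conservative, and clusters of the same size, together with "a correlation of 0.5 between individual measurements over time and a 30% loss to follow-up". The section attributes the figure to a cluster-trial calculator. It does not say whether the calculation was adjusted for baseline or based on change, what cluster-level correlation over time was used, or what reference distribution was used.

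The Study design section puts about 20 participants in each cluster and pairs the clusters: "Within each setting and country, two clusters will be paired, with one allocated to the intervention and one to the wait-list control group". The Statistical analyses section plans maximum-likelihood mixed models with group-by-occasion interactions and with country and setting as fixed effects. It names the test: "Contrasts will compare change between groups from T1 to T2 and T3". It names no baseline constraint, no baseline covariate and no pair effect.

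**The concern.** A power figure is useful only for the test that will be run. With a baseline and a follow-up measurement, a difference in change and a baseline-adjusted difference at follow-up estimate the same effect in a randomised trial, but with different variances. The change contrast is never the more precise of the two, and the gap matters when there are only 12 clusters. If the 90% belongs to the adjusted analysis and the trial tests change, a null result would be read as stronger evidence against a 0.5 SD effect than the design provides.

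**Working it through.** **Inputs.** From the protocol article: 6 clusters per arm, 20 recruited per cluster, 30% loss (20 × 0.7 = 14 completers), ICC 0.05, individual correlation over time 0.5, difference 0.5 SD, two-sided 5%. One quantity is an assumption: the CAC, the correlation over time of the cluster effects, which the article does not give. It is varied here.

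**Formulas** (14 completers per cluster, SD = 1):
- Variance of a cluster mean: V = 0.05 + 0.95/14 = 0.1179.
- Covariance of a cluster's means at T1 and T3: C = 0.05 × CAC + 0.95 × 0.5/14 = 0.05 × CAC + 0.0339.
- ρ = C/V.
- Variance of the baseline-adjusted contrast: (2V/6)(1 − ρ²).
- Variance of the change contrast: (2V/6) × 2(1 − ρ).
- Ratio, change to adjusted: 2/(1 + ρ), which exceeds 1 whenever ρ < 1.
- Power: non-central t, or normal, with non-centrality 0.5/SE.

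**Reproducing the plan's figure.**
- CAC 1: C = 0.0839, ρ = 0.712, adjusted variance 0.01936, SE 0.139. Power is 89.8% on 10 df.
- CAC 0.8: C = 0.0739, ρ = 0.627, adjusted variance 0.02383, SE 0.154. Power is 90.0% with a normal reference.

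So 90% can be obtained from the stated inputs with the full 30% loss, for a baseline-adjusted contrast.

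**The planned change contrast.**
- CAC 1: variance 0.02262, SE 0.150, ratio to adjusted 2/1.712 = 1.17.
- CAC 0.8: variance 0.02929, SE 0.171, ratio 2/1.627 = 1.23.

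A likelihood analysis also keeps the T1 data of participants lost before T3. Generalised least squares with 20 at T1 and 14 at T3 lowers these variances to 0.02092 and 0.02759.

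| Contrast | CAC | 10 df | Normal |
|---|---|---|---|
| Adjusted, 14 completers | 1 | 89.8% | 94.9% |
| Adjusted, 14 completers | 0.9 | 86.4% | 92.5% |
| Adjusted, 14 completers | 0.8 | 83.1% | 90.0% |
| Change, 14 completers | 1 | 84.9% | 91.4% |
| Change, 14 completers | 0.9 | 79.8% | 87.4% |
| Change, 14 completers | 0.8 | 75.0% | 83.2% |
| Change, all 20 baselines | 1 | 87.5% | 93.3% |
| Change, all 20 baselines | 0.9 | 82.4% | 89.4% |
| Change, all 20 baselines | 0.8 | 77.4% | 85.3% |

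Adding T2 data (17 per cluster assumed) moves the 10-df change figures by only about half a point, for example 87.5% to 88.0% at CAC 1.

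**When the change contrast reaches 90%.** With a normal reference the variance must be at most (0.5/3.2415)² = 0.0238. The change variance rises by (4/6) × 0.05 = 0.0333 per unit fall in CAC. With 14 completers, CAC must be at least 1 − (0.02379 − 0.02262)/0.0333 ≈ 0.96. With all baselines kept, it must be at least 1 − (0.02379 − 0.02092)/0.0333 ≈ 0.91. On about 150 individual-level df the thresholds are about 0.97 and 0.92. On 10 df no CAC is enough.

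**Sensitivity cases.** Charging country and setting against the cluster df leaves 7; analysing six pair differences leaves 5. At CAC 1 with 14 completers, the change contrast then gives 81.3% and 75.7%. Reading 0.5 as the total rather than the within-cluster correlation changes results by at most about 2 points.

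**The case against.** The strongest defence has three parts.

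First, the 90% is reproducible, and one route to it uses cluster-based df and the full attrition. That stands: this is not an arithmetic error.

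Second, a model with participant and cluster random intercepts implies CAC 1. The cluster effect then cancels from a change contrast, and individual-level or normal df can be defended, giving 91–93%. That also stands at CAC 1. It is fragile, however. T3 comes six months after the course, and intervention participants are trained together after T1, so cluster effects need not stay constant. If the CAC is below 1 and the right reference has about 10 df, a normal-based test has a true type I error near 8%, so its power is not power at the stated 5%.

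Third, a condensed article may leave the CAC and df to a fuller document. That is fair, and the point does not rest on their absence. It rests on a stated figure and a stated contrast that do not match.

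A reader might also infer that the stated inputs alone yield only 62–85%. They do not: the 62% needs a CAC of 0.5, which the article never gives, and the 85% ceiling discards dropouts' baselines. The simple check that multiplies the whole design effect of 1 + 13 × 0.05 = 1.65 by (1 − 0.5²) gives 83.0% (normal) or 74.7% (10 df), but it too sets the cluster-mean correlation to 0.5, which is CAC 0.5. Nor do the 7-df and 5-df figures describe the planned analysis. Country and setting as time-invariant main effects drop out of a change contrast, no pair effect is named, and the 5-df figure allows no gain from matching.

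**Conclusion.** The point holds as a mismatch between two sections. On like-for-like settings, moving from the baseline-adjusted to the planned change contrast takes power from 89.8% to about 85–87.5% (CAC 1, 10 df), or from 90.0% to about 83–85% (CAC 0.8, normal). With CAC 0.8 and 10 df, the change contrast has about 75–77%. The lower end of each range uses completers only; the upper end keeps all baselines. The change contrast reaches 90% only with a CAC of roughly 0.91–0.97 or more, depending on which baselines and reference are used, and with a normal or individual-level reference.

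These figures rest on equal clusters of 14 completers, the article's ICC and individual correlation, and an assumed CAC range of 0.8–1. They do not show that the sample size is inadequate or that the calculator was misused.

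**What to change.** Choose one of two changes:

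1. Make the primary T3 contrast baseline-constrained (a common T1 mean in both arms) or baseline-adjusted, so that it matches the power calculation. Report power as about 83–90% for d = 0.5 over CAC 0.8–1 on 10 df.
2. Keep the change contrast and restate its power as about 75–87% for d = 0.5 over CAC 0.8–1 on 10 df.

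In either case, state the CAC and degrees of freedom behind the quoted figure, show power over a range of CAC, and use the same small-sample reference in the analysis. Any 7-df or 5-df figures should be labelled as sensitivity cases.

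The cost is a few sentences, plus one change of model specification under the first option. Recruitment and data collection are unaffected. The first option is preferable because it recovers about 3 to 8 percentage points of power on 10 df (90.4% against 87.5% at CAC 1 with all baselines kept; 83.1% against 75.0% at CAC 0.8 with completers only).

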#### Statistical analyses

Statistical analyses will be conducted by a researcher not involved in participant recruitment or intervention delivery and blinded to allocation, following intention-to-treat principles; all participants who consent to participation will be included in the analysis, regardless of intervention completion or follow-up responses. Outcomes will be analysed at the individual level (rather than cluster level). Primary and secondary data will be analysed using mixed-effects models for continuous and binary outcome variables, incorporating interactions between group and measurement occasions. This method takes into consideration the data’s hierarchical structure (ie, the correlation of measurement occasions within participants and within clusters) and uses maximum likelihood methods to generate unbiased estimates even when some participants have missing data, provided that the data are missing at random. Country and setting will be added as fixed effects. Predictors of missingness will be examined using logistic regression, and variables linked to missingness will be added to models as fixed effects. Contrasts will compare change between groups from T1 to T2 and T3. Unless there are substantial imbalances at baseline, between-group effect sizes (Cohen’s d) will be calculated by standardising the differences between follow-up scores by the pooled SD. Otherwise, Cohen’s d will be calculated by dividing the mean change in each group by the pooled SD at baseline. Statistical analyses will be conducted using Stata V.19.^57^

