### Setting and participants

#### Recruitment of clusters

The local research teams in Chile and Argentina will contact alumni offices at universities, personnel departments at healthcare centres and human resources managers in large companies to invite individuals to participate in the study. Representatives from these organisations will be interviewed and provided with a Plain Language Statement prior to participant recruitment and randomisation. Multiple meetings with representatives from each setting are planned in order to minimise the influence of organisational interests on the recruitment of participants. We anticipate conducting one training course per setting in each country with the intervention group (and another at the end with the wait-list group). Each cluster is expected to include approximately 20 participants. No formal pairing criteria will be applied; however, the relative homogeneity of each setting and consideration of education level are intended to contribute to comparability between groups. In addition, potential contamination of groups will be considered (eg, participants in the intervention group sharing what they learnt or training materials with participants in the control group). For example, students pursuing the same degree will be allocated to the same cluster, and participants from the same (or different) areas or facilities will likewise be grouped accordingly, in order to minimise the possibility of participants from different groups having regular contact in the course of their study or work. A summary of the number of clusters per arm, assumed cluster size, cluster types and pairing approach is provided in online supplemental table 1.

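### Country, setting and missingness predictors are planned as fixed effects with no stated occasion interaction, so they adjust level but not the tested change contrasts, and cannot fully correct arm-differential drop-out linked to change

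*Protocol article*

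**What the plan says.** All of the model is in Statistical analyses in the protocol article. Outcomes go into mixed-effects models "incorporating interactions between group and measurement occasions". No other interaction is named. On covariates the text states "Country and setting will be added as fixed effects", and, after a logistic regression to find predictors of missingness, "variables linked to missingness will be added to models as fixed effects". The result is read from change: "Contrasts will compare change between groups from T1 to T2 and T3". Maximum likelihood is said to give unbiased estimates "provided that the data are missing at random". The default effect size is obtained by "standardising the differences between follow-up scores by the pooled SD".

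Study design sets out the allocation: "Within each setting and country, two clusters will be paired, with one allocated to the intervention and one to the wait-list control group". That makes six pairs (2 countries x 3 settings). No pair term is listed, so country and setting are the only terms that could carry the pairing into the analysis. Recruitment of clusters adds "No formal pairing criteria will be applied".

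**The concern.** A covariate effect that is constant over time raises T1, T2 and T3 equally, so it vanishes from a difference between occasions. The plan adds missingness predictors as part of its handling of incomplete data, but tests a quantity that their main effects barely touch. A variable related to both drop-out and gain has to be allowed to act on gain. Otherwise the fitted model does not condition on the information that would make the data missing at random.

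The setting makes this worth settling. The sample size allows for 30% loss, and participants know their arm after randomisation. The incentive to stay also differs by arm: under Data collection and measures, wait-list participants may take the course only after the T3 questionnaire, while intervention participants have already had it. Drop-out that depends on different things in the two arms is therefore plausible, although the document gives no figures for it.

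The same algebra means that differences in gain between countries or settings stay in the error of the contrast, despite allocation within those strata.

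**Working it through.** **Inputs from the protocol article.** Six clusters per arm, about 20 participants each (14 after 30% loss), ICC 0.05, correlation over time r = 0.5, effect 0.5 SD at 6 months. Everything about how drop-out depends on a covariate is my assumption.

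**Scale.** The stated 90% power can be reproduced. Var = 2[1+(m-1)ICC](1-R²)/(km), with R = [m·ICC·CAC + (1-ICC)·0.5]/[1+(m-1)ICC]. The cluster autocorrelation (CAC) is not stated. With m = 14, k = 6, CAC = 0.8: R = (0.56+0.475)/1.65 = 0.627; Var = 2 x 1.65 x 0.607/84 = 0.0238; SE = 0.154; power (normal) 90.0%. With CAC = 1 and 10 df it is 89.8%. The present point does not change this figure. It supplies an SE of about 0.154 as a yardstick.

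**Cancellation.** In a simulated complete data set of 240 people, the T2 and T3 group-by-occasion contrasts were -0.31930878 and -0.2745159 both with and without a covariate main effect. With 30% missing at T3, the T3 contrast moved from -0.3503 to -0.3504.

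**Drop-out bias by hand.** Take two occasions (T1, T3) and a binary covariate X with prevalence 0.5. X has effect a at T1 and a+b at T3, and the fitted main effect is d. Let Δ be the share with X = 1 among intervention completers minus 0.5, with drop-out in the control arm unrelated to X. Under the random-intercept model the estimated T3 mean is the completers' mean plus r times the T1 shortfall of completers, so

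bias = Δ[b + (1-r)(a-d)].

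Without the covariate, d = 0. With its main effect, d lies between a and a+b.
- Level only (b = 0, d = a): bias 0.
- Change only (a = 0, b = 0.4), intervention drop-out 10%/50% by X, control 30%/30%: Δ = 0.25/0.70 - 0.5 = -0.143. Without X: -0.143 x 0.4 = -0.057, an estimate of 0.443. With the main effect and r = 0.5, the bias lies between half of this and all of it (0.029 to 0.057).
- Milder drop-out, 20%/40%: Δ = 0.30/0.70 - 0.5 = -0.071; without X -0.029, an estimate of 0.471; with the main effect 0.014 to 0.029.

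**Fitted models, true effect 0.50.** Large-sample GLS with a participant random intercept, for X omitted / main effect / crossed with occasion: 0.444 / 0.459 / 0.501 for 10%/50%, and 0.470 / 0.478 / 0.498 for 20%/40%. The residuals with the main effect are 0.041 and 0.022. Varying when X acts in the 10%/50% case gives 0.44 to 0.47 with the main effect, a residual of 0.03 to 0.06.

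**A wider set.** Continuous X, three occasions, r = 0.5, about 30% drop-out, log-odds of drop-out 1 per SD of X in the intervention arm only. Bias in the T3 contrast in SD units, compound-symmetric covariance:

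| Effect of X | Omitted | Main effect | Crossed |
|---|---|---|---|
| T3 only, 0.5 | -0.128 | -0.114 | +0.002 |
| T2 and T3, 0.5 | -0.103 | -0.072 | +0.003 |
| Level 0.25, change 0.5 | -0.127 | -0.076 | -0.002 |
| Level 0.5, change 0.25 | -0.089 | -0.040 | -0.001 |
| Level 0.5, change -0.25 | +0.010 | +0.044 | +0.005 |
| Level only, 0.5 | -0.046 | -0.005 | -0.005 |
| Change 0.5, same drop-out in both arms | +0.006 | +0.006 | +0.008 |

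Simulation noise is of the order of 0.005 to 0.008. An unstructured covariance gives the same pattern.

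**Pairing.** Cluster-mean change, 14 per cluster, 40,000 simulated trials. Leaving the strata out of the contrast gives 12 - 2 = 10 df; including country (1) and setting (2) leaves 7.

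| SD of pair differences in gain | Power, strata out | Power, strata in | Type I error, strata out |
|---|---|---|---|
| 0 | 85% | 81% | 5.0% |
| 0.1 | 81% | 79% | 3.7% |
| 0.2 | 70% | 72% | 2.1% |
| 0.3 | 52% | 61% | 0.8% |

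**The case against.** The article does not say that these terms enter only as main effects. Adding something as a fixed effect can simply mean that it is not random, and a separate analysis plan may list interactions. That is fair as far as it goes. But the article names the one interaction it intends, the form of the other terms and the contrast, so main effects is the plain reading and the ambiguity itself needs closing.

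A reader might infer that most drop-out bias stays whatever happens. The document does not support that. It gives 30% loss overall and nothing by arm, and the outcome turns on the mechanism: equal patterns leave nothing to correct, and a predictor of level alone is handled by its main effect. Nor is the missing-at-random sentence false, since it is conditional. The sizes are also modest: 0.022/0.154 = 0.14 and 0.041/0.154 = 0.27 of a standard error.

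A reader might also infer that leaving the pairing out makes the test invalid. It does not. Type I error stays at or below 5%, and with 12 clusters and matching on country and setting alone the simpler contrast can be the more powerful one. That objection stands in full.

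Finally, exact cancellation does not extend to the default Cohen's d, which uses follow-up differences, or to the logistic models for binary outcomes.

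**Conclusion.** The point holds in limited form. As written, country, setting and missingness predictors adjust level and leave the tested linear change contrasts almost untouched. The step meant to protect against drop-out therefore fails in the case where a predictor is tied to change and drop-out depends on it differently by arm. In the fitted examples with a 0.4 SD binary predictor, the residual bias is about 0.02 to 0.06 SD. With a stronger continuous predictor acting on change it is 0.04 to 0.11 SD, and in one scenario the main effect made matters worse (+0.010 to +0.044). All of these sizes rest on assumed effects and drop-out patterns, and the document cannot tell us which applies. Crossing the predictor with occasion removed the bias in every scenario tried. The pairing part is a matter of efficiency with a genuine trade-off and is not an error.

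**What to change.** State in the analysis section that each missingness predictor enters with its interaction with occasion. Alternatively, model follow-up adjusted for the T1 score with these predictors as covariates. Draw the predictors from T1 variables. This is a safeguard, since the text names no post-allocation predictor but does not exclude one. The cost is two further coefficients per single-term predictor (T2 and T3), and no new data.

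For country and setting, say explicitly whether they are crossed with occasion. Crossing them lets the pairing enter the contrast but uses 3 of about 10 cluster-level degrees of freedom. On the figures above it gains power only when the SD of stratum differences in gain is about 0.2 or more. Either choice is defensible if fixed before the data are seen. If no covariate is crossed with occasion, add a sentence that these terms adjust level only and do not protect the change contrasts against arm-differential drop-out linked to change.
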